## Abstract

Liver diseases cause nearly 2 million deaths worldwide each year, with approximately 1 million deaths from cirrhosis complications and another 1 million from viral hepatitis and liver cancer, according to WHO estimates. Liver transplantation (LT) remains the primary curative option, boasting success rates of 85% in the first year and 75% at five years post-transplant. Despite high costs, LT is considered cost-effective, especially for younger patients with active work years remaining. However, post-transplant complications, particularly intrahepatic cholestasis, present notable challenges. This complication arises from factors such as ischemia-reperfusion injury, infections, immunological rejection, and surgical complications, all contributing to impaired bile flow and liver damage. Current medical therapies for post-LT cholestasis are limited, with ursodeoxycholic acid (UDCA) frequently used, despite questionable efficacy. Obeticholic acid (OCA), a potent Farnesoid X Receptor (FXR) agonist approved by the FDA for treating primary biliary cholangitis (PBC), has shown potential benefits in reducing elevated cholestatic liver enzymes. Given its significant effects on liver health, OCA may offer therapeutic value in managing post-transplant cholestasis and improving graft survival.

This randomized controlled trial (RCT) aims to evaluate OCA’s efficacy compared to UDCA in reducing cholestatic injury and enhancing graft function post-LT. The primary outcomes will focus on a 15% reduction in alkaline phosphatase and gamma-glutamyl transferase levels at 3, 6, and 12 months from baseline one month. Secondary outcomes include molecular markers, biliary complications, graft rejection, quality of life, and cost-effectiveness. Results are anticipated to demonstrate that OCA could ameliorate cholestasis, improve graft survival, reduce post-transplant complications, and enhance quality of life, potentially setting a new standard in post-LT care if found beneficial.

## Introduction

Liver diseases cause nearly 2 million deaths worldwide each year, with approximately 1 million deaths from cirrhosis complications and another 1 million from viral hepatitis and liver cancer, according to WHO estimates.
^
1,
2
^ Liver transplantation (LT) is recognized as the primary curative treatment, with success rates reaching 85% in the first year and 75% at 5 years post-transplantation.
^
3
^ In India, over 3000 liver transplants are performed annually. Despite the considerable expense associated with LT, it is considered cost-effective, especially for individuals in their prime years, who have many active work years ahead of them.
^
4,
5
^ However, post-transplant morbidity, particularly intrahepatic cholestasis, presents significant challenges.
^
6
^

Intrahepatic cholestasis is a major complication following liver transplantation, caused by multiple factors. Ischemia-reperfusion injury during organ retrieval and transplantation leads to cellular damage and postoperative cholestasis.
^
7,
8
^ Sepsis from infections worsen cholestasis through inflammatory responses.
^
9
^ Essential post-transplant drugs, including immunosuppressants and antibiotics, can interfere with bile formation, causing liver injury.
^
10,
11
^ Immunological reactions such as T-cell and B-cell-mediated rejection and lymphocytic cholangitis also contribute to cholestasis.
^
12
^ Surgical complications like stenosis or obstruction of the biliary and vascular anastomosis can also result in intra- and extrahepatic cholestasis.
^
13–
15
^

The absence of effective medicines limits the current medical therapy of cholestasis. Although its usefulness is questionable, many practitioners utilize ursodeoxycholic acid (UDCA) as a hepatoprotective drug.
^
15
^ It is usually administered for three months post-transplant at a dose of 10-15 mg/kg thrice daily. In 2016, the FDA approved obeticholic acid (OCA), a strong selective Farnesoid X Receptor (FXR) agonist, to treat primary biliary cholangitis (PBC) in conjunction with UDCA.
^
16,
17
^ Research has demonstrated that over 12 months, OCA, either in combination with UDCA or on its own, dramatically lowers levels of total bilirubin and alkaline phosphatase.
^
18,
19
^ In individuals with advanced liver disease, the FDA has cautioned against administering OCA at doses of 10–50 mg.
^
20
^ Studies comparing OCA’s effects on cholestasis, rejection, regeneration, and cost-effectiveness to the current standard UDCA are being conducted to assess the role of OCA in the postoperative recovery of liver transplant patients.
^
21
^ Our proposed project is a randomized controlled trial between OCA and UDCA, in managing post-liver transplant cholestasis, improving graft survival and overall quality of life.
^
22
^

### Rationale

Following LT, a major morbidity mitigating long-term liver functions is intrahepatic cholestasis due to a multitude of reasons. UDCA remains the first-line pharmacological therapy for most forms of intrahepatic cholestasis.
^
23
^ FXR is a newly detected receptor gene, playing multiple roles in liver homeostasis, including detoxification of bile acid excess, stimulation of bile salt export from hepatocytes, reduction of inflammation, delaying fibrosis, and perhaps may even assist liver regeneration.
^
24,
25
^ Although obeticholic acid was previously approved as a second-line therapy for primary biliary cholangitis, the U.S. Food and Drug Administration withdrew its approval in 2024 following failure to demonstrate confirmatory clinical benefit. Nevertheless, as a potent farnesoid X receptor agonist with well-characterized effects on bile acid synthesis and transport, it remains a biologically relevant therapeutic candidate warranting further investigation in specific cholestatic settings.
^
26
^ Research shows OCA significantly reduces key liver enzymes like alkaline phosphatase, gamma glutamyl transferase and total bilirubin in cholestatic liver disease, though its effects specifically in LT patients have not been well-studied.
^
27,
28
^

This study aims to fill an essential gap by evaluating the efficacy of obeticholic acid compared to ursodeoxycholic acid in managing post-liver transplant cholestasis. By conducting specific biochemical tests to assess cholestasis, this research will provide insights into the effectiveness of OCA relative to the current standard, UDCA.
^
29
^ Additionally, this study will examine the potential effects of OCA on rejection, tissue regeneration, and cost-effectiveness—areas where knowledge is currently limited.
^
30,
31
^ The ultimate goal of this study is to determine whether OCA can emerge as a new standard of care in post-LT management, offering cost-effective solutions to enhance long-term outcomes for liver transplant patients.

### Primary outcomes

The primary endpoint will be the proportion of patients achieving a ≥15% reduction in serum alkaline phosphatase (ALP) and gamma-glutamyl transferase (GGT) levels at 3, 6 and 12 months compared with the one-month post-transplant baseline between the two groups. ALP and GGT is assessed at 6 and 12 months to evaluate the trajectory and durability of response over time.

### Secondary outcomes

•Assessment of biochemical markers (Liver function tests, metabolic profile, CRP, tacrolimus levels).•Molecular markers (fibroblast growth factor 19 (FGF-19), transforming growth factor β (TGF-β) level, Cytokeratin 18 level, Serum autotaxin level, Bile Salt Export Pump levels (BSEP), Plasma bile acid levels.•Biopsy-proven acute or chronic rejection.•Incidence of biliary complications.•All-cause mortality.•Any adverse events.•Death due to acute or chronic rejection.•Quality of life.

## Methods

### Trial design

This is a single-center, open-label, parallel-group randomized controlled trial conducted at a tertiary care liver transplant center.

### Participants

Adult living donor liver transplant recipients who meet the predefined inclusion and exclusion criteria have been enrolled in the study since December 2021.

### Eligibility & exclusion criteria

All adult patients undergoing live donor liver transplantation during the study period are being included. Recipients who are less than 18 years of age, those undergoing deceased donor liver transplants, ABO-incompatible transplants, retransplant cases, those not surviving beyond 30 days, and patients lost to follow-up during the study period, are being excluded. We excluded patients who were randomized into the trial but died within the first 30 days. This decision was based on the fact that early mortality in this period is most commonly attributable to sepsis or technical complications. Including such patients would not be appropriate for evaluating interventions aimed at the management of cholestasis, which usually occur 2 to 3 weeks after surgery. Mortality within 30 days, purely secondary to the adverse effect of the drug, with no other technical (vasculo-biliary), septic or immunological cause is extremely unlikely. Obeticholic acid was administered at a low dose of 5 mg once daily, which represents the standard starting dose used in clinical trials. Published studies have demonstrated acceptable tolerability at this dose, with pruritus being the most commonly reported adverse event and no evidence of treatment-related early mortality.

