**Allocation**

Participants are randomized in a 1:1 ratio using a computer-generated permuted block sequence. Allocation concealment will be ensured using sequentially numbered, sealed opaque envelopes opened by the study pharmacist on postoperative day two.

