**Figure 1. f1:**
[figure not shown]
Flow chart showing study methodology.

We selected a 15% reduction in both alkaline phosphatase (ALP) and gamma-glutamyl transferase (GGT) as our primary biochemical endpoint based on evidence from previous trials in cholestatic liver disease. Specifically, the landmark study by Nevens et al., published in The New England Journal of Medicine (2016), evaluated obeticholic acid in patients with primary biliary cholangitis and used a composite endpoint that included a ≥15% reduction in ALP as part of the therapeutic response criteria.

Although this trial was not conducted in post–liver transplant patients, it provided a strong precedent for using ALP-based endpoints to assess treatment response in cholestatic conditions. We extended this rationale by including GGT alongside ALP, as the combination of these two enzymes provides a more comprehensive and sensitive assessment of cholestasis, particularly in the post-transplant setting where bile duct injury and graft function are dynamic.

Given the lack of clinical trials of OCA in the liver transplant population, this combined biochemical endpoint serves as a reasonable and evidence-informed surrogate marker of response in our study.

Secondary endpoint serum markers are being assessed using an enzyme-linked immunosorbent assay (ELISA) [ELK Biotechnology™] at the centralized biochemistry laboratory. Blood samples collected during the one-month and twelfth-month post-transplant follow-up visits are being used for ELISA testing.

In addition, demographics, patient characteristics, and other critical study details (e.g., medication history, medical history, social habits, family history, and use of other medical systems) are being collected through direct patient or bystander interviews, doctor consultation notes, hospital health information systems, and case records. The collected data is being transcribed into a pre-designed proforma (data collection form) by the investigator.

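### All eligible living-donor recipients are randomised with no enzyme criterion, but only a 15% fall from month 1 counts as response, so stable normal values score as failure

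*Protocol article*

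**What the plan says.** - **Entry** (Eligibility & exclusion criteria): "All adult patients undergoing live donor liver transplantation during the study period are being included". Besides age and deceased-donor grafts, the exclusions read "ABO-incompatible transplants, retransplant cases, those not surviving beyond 30 days, and patients lost to follow-up during the study period, are being excluded". None concerns ALP, GGT, bilirubin or cholestasis.
- **Allocation**: by "sequentially numbered, sealed opaque envelopes opened by the study pharmacist on postoperative day two". The eligibility section refers to "management of cholestasis, which usually occur 2 to 3 weeks after surgery", so the condition usually appears after randomisation.
- **Endpoint** (Primary outcomes): response is summarised as "proportion of patients achieving a ≥15% reduction in serum alkaline phosphatase (ALP) and gamma-glutamyl transferase (GGT) levels at 3, 6 and 12 months". Change is measured from the month-1 value. The text after Figure 1 confirms that both enzymes must fall: "We selected a 15% reduction in both alkaline phosphatase (ALP) and gamma-glutamyl transferase (GGT) as our primary biochemical endpoint". No minimum baseline is set, and there is no rule for a value that is already normal.
- **Aim** (Rationale): "evaluating the efficacy of obeticholic acid compared to ursodeoxycholic acid in managing post-liver transplant cholestasis". The Conclusion also frames the trial around post-transplant cholestasis.

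**The concern.** The responder rule is a pure percentage fall with no floor, applied to people who were not selected for having anything to reduce. Two consequences follow.

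1. **Dilution.** Patients with normal enzymes at month 1 carry little treatment signal. If they are equally common in both arms, they shrink the difference in responder proportions.
2. **Bias against an early effect.** The baseline is taken about four weeks after allocation. The eligibility section discusses drug-related death within 30 days, which implies treatment before month 1. If one drug brings more patients to normal by then, more of its patients have no room for a further fall and are scored as failures.

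The planned conclusion is affected too. The trial would estimate the effect of routine use in all eligible recipients, while the Rationale and Conclusion speak of managing cholestasis.

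**Working it through.** **Plan's own figure.** The Sample size section states 108 per arm, based on a pilot difference in mean ALP and not on a responder proportion, so it makes no allowance for dilution. The printed inputs do not reproduce it. The difference is 12.496 − 5.131 = 7.365 and the pooled SD is √((39.639² + 52.139²)/2) = 46.313, which gives 621 per arm (two-sided 5%, 80% power). That is a separate matter. Here 108 serves only as the planned size.

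**Assumed inputs, not in the documents.** Response rates p among patients with raised month-1 enzymes; share q with normal enzymes; chance response r among those with normal enzymes, equal in both arms.

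**Chance response.** With no true change, the log ratio of two measurements has SD = √2 × log-scale SD, and the threshold is ln 0.85 = −0.1625. The correlation between the two enzymes is taken as 0.5.
- Within-patient CV 10%: SD 0.141, z = −1.15. One enzyme falls by 15% in 12.5% of patients, both in 4.4%.
- CV 25%: SD 0.348, z = −0.47. One enzyme 32.0%, both 17.3%.

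The range of 5% to 15% for r is therefore reasonable.

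**Dilution.** The observed proportion in each arm is (1 − q)p + qr, so the difference between arms is multiplied by (1 − q) whatever r is. Power is Φ{(|d| − 1.96√(2p̄(1 − p̄)/n)) / √(p₁(1 − p₁)/n + p₂(1 − p₂)/n)}, where d is the difference and p̄ the mean of the two observed proportions.

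Example with 50% vs 70%, q = 0.25, r = 0.05:
- Proportions: 0.75 × 0.50 + 0.0125 = 0.3875 and 0.75 × 0.70 + 0.0125 = 0.5375, so d = 0.15.
- At n = 108: (0.15 − 1.96 × 0.0679)/0.0671 = 0.25, giving power of 60%.

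Under the proposed clause r becomes 1, assuming that patients normal at month 1 stay normal. Power at 108 per arm:

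| Response if enzymes raised | q = 0 | q = 25%, as written | q = 25%, with clause | q = 50%, as written | q = 50%, with clause |
|---|---|---|---|---|---|
| 50% vs 70% | 86% | 60% | 67% | 33–35% | 45% |
| 40% vs 60% | 84% | 61–62% | 63% | 35–38% | 40% |
| 30% vs 50% | 86% | 65–66% | 60% | 38–42% | 36% |

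At 120 per arm, the top of the planned range, the as-written figures for 50% vs 70% are 89%, 64% to 65%, and 36% to 38%.

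**Early effect.** Here q differs by arm. Suppose 20% are normal at month 1 on the less effective drug and 40% on the better one, with 60% response among the rest in both arms and 5% chance response.
- As written: 0.80 × 0.60 + 0.20 × 0.05 = 49% against 0.60 × 0.60 + 0.40 × 0.05 = 38%. The better drug looks worse.
- With the clause: 0.48 + 0.20 = 68% against 0.36 + 0.40 = 76%. The order is right.

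**The case against.** Several counter-arguments have weight.

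- **Enrolling all recipients is defensible.** The Rationale also speaks of a new standard of care in post-transplant management, and Expected results mentions preventing damage to the graft. This stands: enrolment need not change, but the objective should match it.
- **A continuous analysis already exists.** The Statistical analysis section compares means between groups at each visit, which needs no responder floor. This stands in part. The analysis is useful support, but it does not correct the classification in the stated primary endpoint. The log scale is a preference.
- **The size is hypothetical.** This stands. The Blinding section describes many recipients as high-MELD and allows four weeks for early fluctuations to settle, but no month-1 distribution of ALP or GGT is given.
- **The clause does not undo dilution.** This stands. It leaves the difference multiplied by (1 − q) and only moves the overall rate. Power rises at 50% vs 70%, changes little at 40% vs 60% and falls at 30% vs 50%.

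A reader might infer that every patient with normal enzymes is scored a failure. The rule does not say that: a fall of 15% in both enzymes within the normal range counts as success. A reader might also want a subgroup with cholestasis defined before the first dose. The protocol does not support it, because it places cholestasis at 2 to 3 weeks and its visit schedule lists no pre-dose ALP or GGT.

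**Conclusion.** The concern holds. The protocol combines entry without an enzyme criterion, allocation on day two and a percentage-fall endpoint with no provision for normal values. Stable normal enzymes, a good course, count as non-response apart from chance falls.

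The loss of power from 86% to about 60% or to 33% to 35% depends on the assumed 50% vs 70% response, 5% to 15% chance response, and a quarter or a half of patients normal in both arms. The reversal against an early effect rests on its own assumed shares, 20% vs 40% normal at month 1. Neither size can be derived from the documents, but the direction of both effects follows from the rule as written. The protocol should be changed before analysis. The reason is correct classification and freedom from bias against early effect, not a general gain in power.

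**What to change.** - Keep enrolment unchanged.
- Define response at each visit as a fall of at least 15% in both ALP and GGT from month 1, or both values at or below the upper limit of normal at that visit.
- Name the between-arm comparison of ALP and GGT levels, preferably on the log scale, as the main supporting analysis.
- Word the objective and conclusion as routine OCA versus UDCA from day two in all eligible living-donor recipients, without a claim about treating established cholestasis.

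**Cost.** Wording changes and one supporting analysis of values already measured at the scheduled visits. The study is still recruiting, so this can be settled before analysis. The downside is a slightly more complex responder definition.

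### Randomised patients who die within 30 days or are lost to follow-up are removed, which breaks the randomised comparison and takes early deaths out of the mortality and safety outcomes

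*Protocol article*

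**What the plan says.** Under Eligibility & exclusion criteria, the protocol article lists among its exclusions "those not surviving beyond 30 days, and patients lost to follow-up during the study period, are being excluded". It then makes clear that the first of these applies after allocation: "We excluded patients who were randomized into the trial but died within the first 30 days". Three reasons are given. Early deaths are mostly septic or technical, cholestasis usually appears two to three weeks after surgery, and a death caused purely by the drug is considered very improbable at the low dose used, given published tolerability.

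Under Allocation, patients are randomised 1:1 in permuted blocks, with envelopes "opened by the study pharmacist on postoperative day two". Under Blinding, the trial is open-label.

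Secondary outcomes include "All-cause mortality", any adverse events, biopsy-proven rejection, biliary complications and death due to rejection. None is restricted to patients alive at day 30. Expected results anticipates fewer biliary complications and lower all-cause mortality on obeticholic acid (OCA).

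**The concern.** Survival to day 30 and completeness of follow-up cannot be known when the envelope is opened. They are outcomes written as eligibility criteria. Removing patients on such grounds gives up the protection of randomisation: the arms remain comparable only if the removals are unrelated to treatment, which the trial should test and not assume.

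Two things are at stake. First, mortality and safety would omit days 2 to 30, so an early imbalance in either direction could not show in those comparisons. Second, the primary responder comparison is biased whenever removals differ by arm and removed patients differ in prognosis. In an open-label trial with different dosing frequencies, and with pruritus named as the commonest adverse event of one drug, loss to follow-up could plausibly depend on arm. The document gives no data on whether it does.

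**Working it through.** **Timing.** Randomisation is on day 2 and the death exclusion runs to day 30, so about 28 of the 30 days fall after allocation. Deaths before day 2 never enter the trial and are not at issue. The loss-to-follow-up exclusion runs through the whole study period, to month 12.

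**The stated reasons against the rest of the article.**
- Cholestasis is said to appear at two to three weeks. That lies inside the removed window.
- The argument sets aside deaths with a technical (including biliary), septic or immunological cause. Yet biliary complications, rejection and death due to rejection are trial outcomes, and OCA is expected to reduce biliary complications. Deaths by these routes are among those the trial should compare by arm.
- The argument relies on tolerability in other settings. The Rationale says of OCA that "its effects specifically in LT patients have not been well-studied". That sentence concerns liver enzymes, but the text after Figure 1 says more generally that clinical trials of OCA in the transplant population are lacking.
- Defending the drug's safety in the first 30 days implies that patients are exposed to it then.

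The plan gives no number of removals, so there is no figure of its own to reproduce. The counts and response rates below are assumptions.

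**Mortality (120 per arm, the upper end of planned recruitment).**

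| Early deaths, OCA vs UDCA | Later deaths | All randomised | After exclusion |
|---|---|---|---|
| 10 vs 4 | 6 vs 6 | 16/120 = 13.3% vs 10/120 = 8.3% (5.0 points) | 6/110 = 5.5% vs 6/116 = 5.2% (0.3 points) |
| 4 vs 10 | 6 vs 6 | 8.3% vs 13.3% (−5.0 points) | 5.2% vs 5.5% (−0.3 points) |
| 6 vs 6 | 6 vs 6 | 12/120 = 10.0% in each | 6/114 = 5.3% in each |

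The rule hides harm and benefit alike. Even with balanced deaths it roughly halves the reported mortality in this example.

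**Primary endpoint, single example (115 per arm, no true effect).** Take 46 responders in each arm (40.0%) and remove 12 vs 4 non-responders:
- OCA: 46/(115 − 12) = 46/103 = 44.7%
- UDCA: 46/(115 − 4) = 46/111 = 41.4%
- Spurious difference: 3.2 points. Its standard error is √(0.447·0.553/103 + 0.414·0.586/111) = 6.8 points, so the bias is about half a standard error.

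**Primary endpoint, type I error (120 per arm, no true effect).** If true response is p and a fraction r of an arm is removed, all non-responders, the observed response is p/(1 − r). Type I error is for a two-sided 5% test under the normal approximation.

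| p | Removed, OCA vs UDCA | Observed response | Bias | Type I error |
|---|---|---|---|---|
| 60% | 5% vs 5% | 63.2% vs 63.2% | 0 | 5% |
| 60% | 10% vs 5% | 66.7% vs 63.2% | 3.5 points | 8.5% |
| 60% | 15% vs 5% | 70.6% vs 63.2% | 7.4 points | 21% |
| 50% | 10% vs 5% | 55.6% vs 52.6% | 2.9 points | 7% |
| 50% | 15% vs 5% | 58.8% vs 52.6% | 6.2 points | 15% |

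**Numbers left.** Against the stated minimum of 108 per arm, recruiting 110 to 120 allows 2 to 12 removals per arm: 1 − 108/110 = 1.8% and 1 − 108/120 = 10.0%. The 108 is used here only as the plan's own benchmark.

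**The case against.** The best argument concerns the primary endpoint. It is a change from a one-month baseline, and a patient who dies before month 1 has no baseline and hence no percentage change. Counting that patient as a non-responder is a choice of estimand and not the only defensible one. This stands: for the primary endpoint alone, the authors' reasoning has some force. It has none for mortality, adverse events, rejection or biliary complications, which need no one-month baseline.

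The illustrations use assumed counts, and some effects are small. The 3.2-point bias is half a standard error, and 10 vs 4 deaths out of 115 per arm gives a Fisher p of 0.17, so it would not be conclusive even if fully counted. That is correct. The figures show what the rule can do, not what has happened. An imbalance short of significance is still one that a safety review should see.

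Loss to follow-up is the weaker half. The article says outright that patients were randomised only for the 30-day deaths; for lost patients this follows from the day-two allocation. The method for missing data may properly sit in an analysis plan that is not shown. But the article does not leave the matter open: it says such patients are excluded, and an analysis plan that kept them would contradict it.

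Finally, no section states in words that early deaths are left out of the mortality outcome, and the authors disclose the exclusion openly. The omission is an inference, but a direct one, since the patients are excluded from the trial without exception.

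**Conclusion.** The concern holds. The article fixes two post-randomisation exclusions, and as written they make the mortality and safety comparisons unreliable as randomised evidence and expose the primary comparison to bias. That conclusion rests on the text and the day-two allocation, not on any assumed number.

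The size and direction of bias cannot be derived from the document. Equal removals of like patients leave the comparison unbiased. If 10% to 15% of one arm and 5% of the other are removed, all of them non-responders, and true response is 50% to 60%, the spurious difference is about 3 to 7 points and the type I error about 7% to 21%. For mortality, a 5-point difference arising before day 30 would shrink to about 0.3 points under the assumed counts. This must be corrected before analysis.

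**What to change.** 1. Delete 30-day death and loss to follow-up from the exclusion criteria, and state that every randomised patient is analysed in the assigned arm.
2. Count all-cause mortality, adverse events, rejection and biliary complications from the day of randomisation, and report days 2 to 30 by arm.
3. For the primary endpoint, count death or graft loss before the assessment as non-response. This also settles the missing one-month baseline for early deaths.
4. Handle loss to follow-up by a prespecified method, for example multiple imputation, with a sensitivity analysis that counts lost patients as non-responders.
5. Keep the 30-day survivors as a labelled sensitivity analysis, so that the question the authors have in mind is still answered.
6. Retrieve allocation, dates and events for patients already removed, and report their numbers by arm.

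**Cost.** An amendment while recruitment is still open, and a records search at one centre. Some patients lost to follow-up will have no retrievable outcome, which is why item 4 is needed. Counting early deaths as non-response dilutes the primary effect slightly: if a fraction d of each arm dies before assessment, a response difference among survivors is multiplied by 1 − d, so an assumed 5% turns a 20-point difference into 19 points.
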